## Abstract

**Background:**

Multimorbid older adults suffering from a long-term health condition like depression, diabetes mellitus type 2, dementia or frailty are at high risk of losing their autonomy. Disability and multimorbidity in the older population are associated with social inequality and lead to soaring costs. Our local, collaborative, stepped and personalised care management for older people with chronic diseases (LoChro-Care) aims at improving outcomes for older multimorbid patients with chronic conditions whose social and medical care must be improved.

**Methods:**

The study will evaluate the effects of LoChro-Care on functional health, depressive symptoms and satisfaction with care, resource utilisation as well as health costs in older persons with long-term conditions. The trial will compare the effectiveness of LoChro-Care and usual care in a cross-sectoral setting from hospital to community care. We will recruit 606 older adults (65+) admitted to local hospital inpatient or outpatient departments who are at risk of loss of independence. Half of them will be randomised to receive the LoChro-Care intervention, comprising seven to 16 contacts with chronic care managers (CCM) within 12 months. The hypothesis that LoChro-Care will result in better patient-centred outcomes will be tested through mixed-method process and outcome evaluation and valid measures completed at baseline and at 12 and 18 months. Cost-effectiveness analyses from the healthcare perspective will include incremental cost-effectiveness ratios.

**Discussion:**

The trial will provide evidence about the effectiveness of local, collaborative, stepped and personalised care management for multimorbid patients with more than one functional impairment or chronic condition. Positive results will be a first step towards the implementation of a systematic cross-sectoral chronic care management to facilitate the appropriate use of available medical and nursing services and to enhance self-management of older people.

**Trial registration:**

German Clinical Trials Register (DRKS): DRKS00013904; Trial registration date: 02. February 2018.

## Background

In Western countries, 65% of people aged 65–84 years are living with at least two long-term health conditions, rising to 82% of those aged ≥85 years [1]. In Germany, 58% of female and 55% of male older persons aged ≥65 reported at least one chronic disease in 2012 [2]. Late life depression [3], diabetes mellitus type 2 [4, 5], dementia [6] and frailty [7] increase the risk of functional disability in daily living. As chronic diseases and functional decline are often interrelated, old and very old people with multimorbidity are at high risk of losing their autonomy [8, 9]. Disability and multimorbidity in the older population represent a substantial burden [10] and lead to soaring costs [11]. Indeed, in Germany, persons with multiple chronic diseases have twice as many general practitioner contacts per annum as people without multimorbidity (36.3 versus 15.9) [12]. The increasing prevalence of comorbid long-term conditions is associated with growing rates of preventable and expensive complications.

In Germany, medical and nursing services such as hospital discharge planning [13], counselling of patients and caregivers [14], disease management programs [15], geriatric medical centres [16] and case management for single diseases in primary care settings [17, 18] are well established. However, a systematic approach to cross-sectoral chronic care management is lacking. Such an approach should efficiently guide older people with multimorbidity through the field of fragmented medical and nursing services, and effectively enhance their self-management and their use of informal support networks.

A recent analysis of care delivery in long-term conditions strongly recommended efforts to support the concept of “activated” patients, i.e. patients who are competent in (1) enhanced self-management, (2) identifying and using informal support capacities, and (3) appropriately utilising formal regional health care services [19, 20].

Systematic reviews of randomised controlled trials have yielded mainly moderate evidence suggesting that complex interventions including care and case management are feasible and effective in older people with depression [21, 22], diabetes mellitus type 2 [23, 24], and dementia [25, 26], and those at risk of losing their independence at home [27, 28]. However, for patients with multimorbidity, there is only a limited body of evidence on health outcomes and the cost-saving potential of enhanced care coordination in cross-sectoral chronic care, as shown by systematic reviews [29–31], cost analyses [32, 33], and as confirmed by a current Cochrane review [34] and a recent JAMA editorial [35].

## Study aim and objectives

Older people with multimorbidity frequently experience insufficiently coordinated care. Therefore, the project aims to improve the coordination and performance of their cross-sectoral routine health care and address the evidence gap between mono-disease approaches and complex collaborative chronic care in old and very old people with multimorbidity. In this respect, the objective of the trial is to evaluate the effectiveness of local, collaborative, stepped and personalised care management for older people with chronic diseases (LoChro-Care). The programme is designed to improve functional health, depressive symptoms, satisfaction with care, and health resource utilisation.

We hypothesise the following improvements, to be tested in comparison with usual care: (1) LoChro-Care will result in better functional health as defined by greater independence in activities of daily living. (2) LoChro-Care will more effectively reduce depressive symptoms. (3) LoChro-Care will improve satisfaction with care. (4) LoChro-Care will lead to a more appropriate utilisation of health and nursing care services in terms of decreased emergency hospitalisations, reduced non-elective hospital days and nursing home admissions, more adequate use of informal and formal community services and enhanced disease self-management abilities, and will thus contribute to health care cost savings. (5) Positive LoChro-Care effects will occur directly after the 12-month intervention and will be maintained for at least an additional six months after the intervention.

## Methods/design

### Trial design/setting

The present study will be conducted within the routine care context and is designed as a prospective, two-group usual care controlled trial with 1:1 randomisation on the participant level. Participants will be recruited from all for geriatric patients relevant inpatient and outpatient units of the Medical Center – University of Freiburg, especially the emergency unit. During the 18-month observation period, the chosen endpoints will be measured three times (at baseline, after 12 months and after 18 months). Participants in the intervention group will be supported by a chronic care manager (CCM) over a period of 12 months. The study will be implemented according to CONSORT guidelines (see Fig. 1).

**Fig. 1 Fig1:**
[figure not shown]
Trial Design

LoChro is a cooperation between several departments from the Medical Center – University of Freiburg, the Albert-Ludwig-University of Freiburg, the Catholic University of Applied Sciences Freiburg, the University of Education Freiburg and the recruiting hospitals. There is extensive expertise in care management and research in the fields of geriatric, psychiatric, internal and general medicine as well as in gerontology, education, psychology, social work and health services research.

### Eligibility criteria

The target population comprises geriatric patients admitted to relevant inpatient and outpatient units of the Medical Center – University of Freiburg, aged ≥65 years and residing in or near Freiburg. Patient records will be checked for the presence of these inclusion criteria. Eligible patients will be screened using the “Identification of Seniors at Risk Screening Tool” (ISAR), which has proven to be sensitive in German emergency departments to identify older persons at risk of unplanned readmissions, institutionalisation and need for nursing care [36]. The ISAR tool takes less than five minutes to complete and includes only six simple questions, which are easy for patients or caregivers to answer. Thus, it is feasible to administer. ISAR scores range from 0 (no risk) to 6 (very high risk); persons with an ISAR score of 2 or more are considered to be frail multimorbid patients at risk, and will thus be included in the study. Exclusion criteria are: (1) terminal medical conditions, (2) lack of basic German-language skills or no German-speaking caregiver available, and (3) not residing in the region.

### Intervention group

LoChro-Care follows the ARIADNE principles for the management of multimorbidity [37]. These are: (1) a thorough assessment of interactions between the patient’s conditions, treatments, constitution, and context; (2) a prioritisation process of multiple health problems that takes into account the patient’s preferences, and (3) individualised management that utilises the best options for care and services. The personalised, stepped, cross-sectoral and collaborative LoChro-Care programme will be provided by a qualified nurse who specialises in health education or a social worker acting as CCM. They will be backed up by an interdisciplinary geriatric team, which will provide bi-monthly supervision and can be contacted in the case of urgent need for action. LoChro-Care will be initiated directly after the patients’ discharge from inpatient treatment and includes seven to 16 contacts within a 12-month period.

#### LoChro-care: Key agents and core elements

Novel aspects of LoChro-Care are reflected in the combination of the following approaches within one connected concept: (1) enhancing self-management based on stepped care plans delivered in plain language, which are understandable and foster easy communication between the patients or caregivers and service providers, (2) facilitating the appropriate use of informal support and the use of lay helpers if necessary, (3) supporting the CCM through an interdisciplinary geriatric team, (4) providing the CCM with selected online information on local geriatric services and (5) evaluating the stepped care plans and the spectrum of local geriatric services in its entirety to generate a best practice guideline for regional stepped collaborative care.

#### Implementation and time schedule of the intervention

After receiving the contact details, the CCM will arrange an appointment with the patient at the patient’s home for approximately one week after discharge. The assessment of the questionnaires summarised in Table 1 and individual interviews will form the basis to establish an individual care plan, which will be discussed and decided upon with the patient within two weeks after the first contact. The individual care plan consists of one or more of the following steps: (1) If the existing support by the general practitioner and family or other informal caregivers is sufficient, the CCM will compile, explain and deliver an individualised care plan including information about enhanced self-management and about geriatric outpatient services which are relevant and accessible to the patient. The CCM can choose relevant information about regional geriatric services from an internal project database including links to profiles and contacts. The CCM will encourage the patient to communicate the care plan to all informal and formal care partners. (2) If the patient suffers from cognitive impairment, the CCM intervention will involve the primary caregiver. (3) If there is no primary caregiver and other informal support is lacking, the CCM will establish contact with lay helpers who can serve in a supporting role. (4) If contacts with a general practitioner have been too infrequent or non-existent, the CCM will help to establish this provider relationship with adequate frequency of contact. (5) If the medication list reveals uncertainties for the patient or no medication list exists, the CCM will encourage the patient to get in touch with his/her general practitioner to work on medication problems. (6) If further formal care is needed, the CCM will help to contact the general practitioner and to establish contact with local geriatric services. Examples of local services involved are nursing day care, outpatient services, geriatric outpatient rehabilitation, housing agencies or private practices for physiotherapy or occupational therapy as well as further psychosocial facilities. Four weeks after the second contact, all planned steps will be monitored and discussed with the patient at his/her home. If no personal contact is required, the next three contacts will take place through telephone calls, in which the CCM discusses possible needs for care plan changes with the patient. The final “closing” contact will take place 50/51 weeks after baseline at the patient’s home and will consist of reflections on achievements as well as a summary of recommendations for future care. Additional contacts to this standard intervention are possible in the case of depression or diabetes. For depression, six additional contacts (at home and via telephone) will take place, in which patients are trained in problem-solving techniques. This method has proven successful in numerous depression trials [38, 39]. For diabetes as a present condition, three additional contacts at the patient’s home or via telephone are possible. These contacts will include diabetes-related self-management issues. Details about the sequence of intervention sessions can be found in Fig. 2. To ensure treatment fidelity, the CCM will receive regular specialist counselling by a geriatrician and by a study team member of the University of Education.

**Table 1 Tab1:** LoChro outcome measures, instruments, and times of assessment

Time of assessment (months)	T_0_ (0)	CCM-session 1	T_1_ (12)	T_2_ (18)
Primary outcome				
Functional health (WHODAS 2.0)	X		X	X
Depression (PHQ-9)	X		X	X
Secondary outcomes				
Satisfaction with care (PACIC)	X		X	X
Ressource utilisation (FIMA)	X		X	X
STOPP/START criteria	X		X	X
Health-related quality of life*	X		X	X
Satisfaction with life (Kurzskala L-1)	X		X	X
Intervention group only				
Daily Functioning (Barthel-Index)		X		
Daily Functioning (IADL)		X		
Cognition (MMSE)		X		
Mood (PHQ-9)		X		
Alcohol Use (Audit C)		X		
Mobility (SPPB)		X		
Medication Management*		X		
Individual Interview on patient’s preferences and care situation*		X		

AUDIT-C: Alcohol Use Disorders Identification Test-Consumption; Barthel-Index: daily functioning in older people; FIMA: Fragebogen zur Erhebung von Gesundheitsleistungen im Alter; IADL: Instrumental Activities of Daily Living; Kurzskala L-1: single item scale on satisfaction with life; MMSE: Mini-Mental-State-Examination; PACIC: Patient Assessment of Chronic Illness Care; PHQ-9: Patient Health Questionnaire; SPPB: Short Physical Performance Battery; Stopp/Start: Stopp/Start criteria for potentially inappropriate prescribing in older people; WHODAS 2.0: World Health Organization Disability Assessment Schedule 2.0; *: self-constructed items

**Fig. 2 Fig2:**
[figure not shown]
Sequence of intervention sessions provided by the CCM

### Control group

Patients in the control group will receive usual cross-sectoral care management for old and very old people with multimorbidity at hospital discharge, including a medical referral letter to the patient’s general practitioner and, if indicated, referral to inpatient or outpatient rehabilitation or to outpatient nursing services or nursing homes.

### Outcome measures and assessment

#### Primary and secondary outcome

We reviewed publications on patient-centred outcomes as outlined in the PCORI Methodology Report [40], drew on systematic reviews on core outcome sets as suggested by the international COMET Initiative [41] and analysed reported outcomes from clinical trials in patients with multimorbidity. Based on our analysis of this literature, we conclude that outcomes with the highest relevance for the affected patients are (1) functional health in terms of daily activities (including cognitive and physical functioning), (2) mood (including depression) and (3) satisfaction with care. From a health care perspective, (4) resource utilisation, health care costs and appropriateness of medication plans will be evaluated. Thus, our evaluation plan encompasses both the individual and the health care perspective. We will use instruments that are already established and validated in German populations: The primary outcomes functional health and depression will be assessed with the “WHO Disability Assessment Schedule 2.0, WHODAS” [42] and the “Patient Health Questionnaire, PHQ-9” [43]. The secondary outcomes satisfaction with care, resource utilisation and medication appropriateness will be assessed with the “Patient Assessment of Chronic Illness Care, PACIC” [44], the “Fragebogen zur Inanspruchnahme medizinischer und nicht-medizinischer Versorgungsleistungen im Alter, FIMA” (questionnaire on the use of medical and non-medical services in old age) [45] and the Stopp/Start criteria [46] (see Table 1). Following TOPICS-MDS [47], quality of life and satisfaction with life [48] will additionally be assessed, each by a single-item scale.

In the intervention group, further instruments will be applied (see Table 1). These instruments, as well as the individual CCM interviews, form the basis to develop the individualised and personalised care plans; they are not part of the primary evaluation plan but can be used for additional analysis.

#### Assessment

The chosen endpoints will be measured at baseline and at 12 and 18 months using valid and reliable outcome assessment instruments as described above. We chose feasible and brief patient-reported outcomes in order to evaluate the participants’ perspective and to motivate the patients to become involved through self-reflection and feedback. If necessary, proxy versions of particular/single assessment instruments for caregivers will be used to avoid missing data, e.g. in persons with severe dementia. For proxy assessment, we will only use those instruments which do not require introspection and can thus be rated by caregivers. Additionally, the medication regimens for all enrolled patients will be recorded at baseline and at both follow-up time points.

#### Sample size and power calculation

Based on dropout rates of about 20% in our previous studies and small effects of case and care management on functional health, we hypothesise a Standard Mean Difference of 0.3 to be detected. We calculated a sample size of 606 persons to be randomised at baseline and 242 patients in each arm to be assessed at 12 months (one-sided t-test, significance level 0.05, 95% power, computed for per-protocol analysis, assumption 20% dropout at month 12).

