### Statistical analyses

The statistician will perform an intention-to-treat and per-protocol analysis of the outcome assessment scores at baseline and 12- and 18-month follow-up (dependent variables), adjusting for baseline group differences (independent variables). The hypotheses claim superiority of the intervention group over the control group with respect to the two outcomes (functional health (WHODAS) and depression (PHQ-9)) at 12- and 18-month follow-up. As we will use a composite endpoint of the two primary outcomes (sum of z-score normed component measures), no adjustment of the significance level is necessary. Subgroup analysis will be conducted to reveal group differences in intervention effects between patients with serious versus slight health-related strain. Groups will be classified by an ISAR score of > = 3 versus < 3. Furthermore, secondary outcomes (satisfaction with care, resource utilisation, medication appropriateness) will be analysed. The assumption of ´missing at random` is assumed for the problem of missing data. The fully conditional specification method (an iterative Markov chain Monte Carlo method) will be applied for the imputation of missing data. Dropout analysis will be performed comparing all baseline and follow-up data of completers and dropouts.

In exploratory analyses of all intervention cases, structural equation models will be used, including variables of three dimensions: (1) patient baseline characteristics, (2) CCM treatment procedures as actually carried out and (3) pre-post differences on outcome assessment scores. Through these analyses, we intend to identify possible interactions between characteristics of patients and treatment performance and to deepen our understanding of how the treatment might work and for which patients it can work best.

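### The SMD of 0.3 behind the 95% power is justified for functional health only, while the primary test is a WHODAS plus PHQ-9 composite that also cannot decide hypotheses 1 and 2 separately

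*Protocol article*

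**What the plan says.** The section on sample size and power calculation gives the planning effect as "small effects of case and care management on functional health, we hypothesise a Standard Mean Difference of 0.3 to be detected". The test is specified as "one-sided t-test, significance level 0.05, 95% power, computed for per-protocol analysis, assumption 20% dropout at month 12", and the result is "We calculated a sample size of 606 persons to be randomised at baseline and 242 patients in each arm to be assessed at 12 months". That section does not mention a composite, an effect on depression, or a correlation between scales.

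The section on statistical analyses defines the variable tested: "we will use a composite endpoint of the two primary outcomes (sum of z-score normed component measures"). From this it concludes that "no adjustment of the significance level is necessary". The same paragraph words the superiority claim for both outcomes, at 12 and at 18 months.

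The study aims state the two outcomes as separate hypotheses. The first is that "LoChro-Care will result in better functional health as defined by greater independence in activities of daily living"; the second is a greater reduction in depressive symptoms. Table 1 lists WHODAS 2.0 and PHQ-9 each as a primary outcome.

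**The concern.** Two linked questions arise.

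First, the variable for which the effect is justified is not the variable tested. An SMD of 0.3 on WHODAS becomes an SMD of 0.3 on the composite only for particular values of the PHQ-9 effect and the correlation. A PHQ-9 effect smaller than the functional effect is possible on the protocol's own text. Eligibility rests on age, residence and an ISAR score of 2 or more, with no depression criterion, and the six additional problem-solving contacts are for patients with depression. If power is well below 95%, a null result could be read as stronger evidence against benefit than it is.

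Second, the composite is the stated reason for not adjusting alpha, yet the claims are made for each outcome. One test of a sum answers one question: whether the sum differs. If only one component moves, a positive result could still be reported as better function and better mood.

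**Working it through.** **Inputs from the protocol article.** SMD 0.3, one-sided alpha 0.05, power 95%, 242 per arm at 12 months, 606 randomised, and "assumption 20% dropout at month 12" (all from the sample size section); a "two-group usual care controlled trial with 1:1 randomisation on the participant level" (trial design section).

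**Assumed, not in the document.** The PHQ-9 SMD (dPHQ), shown from 0 to 0.3, and the within-arm correlation r between WHODAS and PHQ-9, shown from 0.3 to 0.7. SMDs are signed so that positive means benefit.

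**Step 1: the protocol's own figure.** With the noncentral t distribution, df = 2n − 2 and noncentrality 0.3·√(n/2), 241 per arm gives power 0.9499 and 242 per arm gives 0.9506. Dropout: 242/0.8 = 302.5, rounded up to 303 per arm, so 606 in total. Both figures reproduce; there is no arithmetic slip.

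**Step 2: effect size of the composite.** With each component scaled to unit SD, the sum has mean difference dWHODAS + dPHQ and variance 2(1 + r). Hence

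d_composite = (dWHODAS + dPHQ) / √(2(1 + r)).

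**Step 3: power of the same unadjusted one-sided t-test at 242 per arm, with dWHODAS = 0.3.** Each cell gives the composite SMD, then power.

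| dPHQ | r = 0.3 | r = 0.5 | r = 0.7 |
|---|---|---|---|
| 0 | 0.186; 65.5% | 0.173; 60.2% | 0.163; 55.7% |
| 0.1 | 0.248; 86.0% | 0.231; 81.4% | 0.217; 77.0% |
| 0.2 | 0.310; 96.1% | 0.289; 93.7% | 0.271; 90.9% |
| 0.3 | 0.372; 99.3% | 0.346; 98.5% | 0.325; 97.3% |

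**Step 4: break-even.** Setting d_composite = 0.3 gives dPHQ = 0.3·(√(2(1 + r)) − 1), which is 0.184, 0.220 and 0.253 at r = 0.3, 0.5 and 0.7.

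**Step 5: sensitivity to baseline adjustment.** If the baseline composite is a covariate with baseline-to-follow-up correlation b, the effective SMD is d_composite/√(1 − b²). The document gives no b. For assumed b of 0.5 to 0.7 and r of 0.3 to 0.7, power at dPHQ = 0.1 becomes about 87% to 98%, and at dPHQ = 0 about 66% to 89%. The break-even dPHQ falls to 0.12 to 0.18 at b = 0.5 and to 0.05 to 0.10 at b = 0.7.

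**Step 6: what a significant composite proves.** The row dPHQ = 0 can be read a second way. If WHODAS improves by 0.3 and PHQ-9 not at all, the unadjusted composite is still significant with probability 55.7% to 65.5%. Anyone who takes that result as support for hypothesis 2 would be wrong that often, not 5% of the time. By symmetry the same holds for hypothesis 1 if only PHQ-9 improves by 0.3.

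**The case against.** The strongest reply is that the sample size section does not tie 0.3 to WHODAS alone. It can be read as choosing a target SMD for the primary variable, with functional-health findings as the anchor. On that reading the 95% is right for the composite. This stands as a possible reading, so the documents do not support saying that the stated 95% is wrong. They support saying that the powered variable is not named and that its justification covers only one of the two components.

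A reader might also infer that the trial is badly underpowered, at about 56%. The documents do not support that. The figure needs no effect on depression together with an assumed r of 0.7, and it ignores covariates. The protocol expects a depression effect: it cites evidence for care management in older people with depression, describes problem-solving training as successful in depression trials, and states hypothesis 2. If the depression effect matches the functional one, the unadjusted composite has 97% to 99% power, more than claimed. The analysis section also plans adjustment for baseline differences, which would raise every figure in the table if baseline scores are covariates.

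On the second part, component reporting and test order are often left to an analysis plan, which is not shown here. That answers any complaint of omission. It does not answer the conflict in the text itself, where one sum is tested, alpha adjustment is waived for that reason, and superiority is still worded for both outcomes.

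**Conclusion.** The concern holds as a mismatch between the endpoint tested and the basis of the power figure, not as an arithmetic error. The figures of 242 per arm, 606 in total and 95% are correct for a single endpoint with SMD 0.3. If 0.3 is the WHODAS effect, the unadjusted composite keeps 95% power only when the PHQ-9 SMD is at least about 0.18 to 0.25. Any shortfall is modest at a PHQ-9 SMD of 0.2 and material at 0.1 or below. These statements rest on assumed r of 0.3 to 0.7 and on the protocol's unadjusted one-sided t-test.

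The second part needs no assumption about effect sizes and carries more weight. Whatever 0.3 refers to, a significant composite establishes neither hypothesis 1 nor hypothesis 2, nor superiority on both outcomes. Because neither part calls for a change in sample size, this should be fixed but does not threaten the trial.

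**What to change.** Keep 606. In the sample size section, do one of two things: state that the SMD of 0.3 refers to the composite and justify it for that variable, or replace the single 95% with a short table of composite power over the PHQ-9 effect (0, 0.1, 0.2, 0.3) and r (0.3 to 0.7), with these labelled as assumptions. Say whether the figures are before or after baseline adjustment.

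In the statistical analyses section, set a fixed test order at month 12, since the protocol has none: the composite, then WHODAS, then PHQ-9, each at the full level and stopping at the first failure. Claim hypothesis 1 or 2 only from its own component test, and reword the superiority claim to match.

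The cost is a paragraph and a restated figure, with no patients added and no alpha spent. There are two downsides. The power figure becomes conditional and may look less favourable. If WHODAS fails, there can be no confirmatory PHQ-9 claim; and even when its test is reached, PHQ-9 alone has only about 71% unadjusted power at an SMD of 0.2 with 242 per arm.
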